## Abstract

**Background:**

Severe acute pancreatitis complicated by acute respiratory distress is a common cause of intensive care unit (ICU) admission. These patients are at risk of a decline in physical activity due to bed rest. Neuromuscular electrical stimulation (NMES) has been recommended for ICU patients to strengthen muscles, but its effects on muscle atrophy, respiratory function, multiple organ dysfunction, and functional status of these patients remain to be proven.

**Methods:**

Patients (*n* = 80) will be prospectively randomized into an NMES group and a control group. The NMES group will receive NMES for 1 h per day for 7 days, and both the control and NMES groups will receive usual care. The efficacy will be assessed by an experienced physiotherapist and sonographer who will be blinded to the patient’s group assignment. Muscle power assessment (MRC scale), lower extremity circumference, grip strength, activities of daily living (Barthel index), and Marshall scores will be measured at baseline and posttreatment. The functions of the diaphragm assessments will be measured daily. Barthel index measurements will be followed up in the 1st month, 3rd month, and 6th month after discharge.

**Discussion:**

The trial will explore the effectiveness of NMES in functional status and diaphragm function in patients with SAP complicated with ARDS. The results of this trial will provide strong evidence of the efficacy of NMES in treating SAP patients with ARDS.

**Trial registration:**

This trial has been registered at the Chinese Clinical Trial Registry, and the registry name is “Effectiveness of neuromuscular electrical stimulation in severe acute pancreatitis complicated patients with acute respiratory distress syndrome: study protocol for a randomized controlled trial,” URL: https://www.chictr.org.cn, numbered ChiCTR2300068995. Date of Registration: 2023-03-03.

**Supplementary Information:**

The online version contains supplementary material available at 10.1186/s13063-023-07642-0.

## Introduction

Acute pancreatitis (AP) is a common disease in clinical practice due to an inflammatory disorder of the pancreas [1]. Twenty percent of AP patients may develop systemic inflammation leading to organ failure, defined as “severe acute pancreatitis (SAP)” [2–4]. Previous studies have demonstrated that the lung is the commonly damaged target organ caused by early induction of systemic inflammatory response syndrome (SIRS) in SAP [5]. One third of patients with severe pancreatitis develop acute lung injury (ALI) and ARDS in the first week [6], and these complications are responsible for high mortality and ICU admission [7–9]. In addition, blood purification, respiratory support, and sedation are common treatments but cause long-term bed rest for SAP patients with ARDS. Patients who stay in bed can experience muscle atrophy in the early stage. Studies have shown that the rectus femoris cross-sectional area decreases rapidly during the first week of bed rest; furthermore, muscle atrophy is more pronounced in patients with multiorgan failure [10, 11]. Muscle wasting is associated with reduced muscle strength and exercise capacity. The decline in exercise capacity is related to poor quality of life, increased mortality, and financial burden on healthcare [12–14]. Early intervention to reduce muscle wasting during the first week of bed rest in patients with SAP complicated with ARDS is urgently needed.

Several protocols have been proven to be feasible interventions to prevent muscle wasting in ICU patients. However, early mobilization and physical exercise are limited due to sedation, dyspnea, increased intra-abdominal pressure, or blood purification for the acute phase of SAP. NMES is an effective and common intervention to prevent muscle atrophy in clinical practice. NMES sends electrical impulses transcutaneously to motor neurons, causing involuntary muscle contractions. Studies have revealed that NMES is a convenient, safe, and beneficial intervention for early immobilization in the ICU [15, 16]. In patients who prolonged bed rest and inactivity, some studies have found that NMES can reduce muscle atrophy and preserve muscle strength [17, 18]. Furthermore, NMES can preserve fiber cross-section (CSA) and higher gene expression for myosin heavy chains [19, 20]. However, other studies have found that NMES is not a useful adjunct to revert muscle wasting and muscle layer thickness, especially for acute patients in the ICU [21–23]. In addition, Gutiérrez-Arias et al. revealed that NMES may reduce the duration of invasive mechanical ventilation for ICU patients, but the mechanism of the impact of NMES on ventilator weaning is unclear [24]. At present, there is insufficient evidence indicating that NMES intervention results in clinically important changes in muscle strength, respiratory function, and functional status for SAP patients with ARDS.

This trial aimed to investigate the effectiveness of NMES on function status outcomes in patients with SAP complicated with ARSD and to investigate the effects of NMES on muscle atrophy, diaphragm function, multiple organ dysfunction, and quality of life after discharge.

## Method

### Study design

The overall objective of this trial is to explore the superior effects of NMES on preventing muscle wasting in patients with early SAP complicated with ARDS compared with sham intervention. We designed a randomized, prospective, single-blind trial (evaluator) because stimulation and contraction evoked during NMES therapy cannot be blinded to patients. Eighty patients who meet the inclusion criteria will be randomly divided into the NMES group and the control group at a ratio of 1:1. All participants will complete data collection and follow-up interviews. Assessment and treatment will be performed by a physician and therapist with 5 years of clinical experience, and diaphragm ultrasound evaluation will be performed by trained sonographers. Participants’ clinical assessments will be performed at baseline and 7 days postintervention, diaphragm ultrasound assessments will be performed daily, and follow-up assessments will be completed at months 1, 3, and 6 after discharge. The NMES group will receive neuromuscular electrical stimulation intervention and usual care for 7 days within 48 h of ICU admission, and the control group will receive the usual care only. The flowchart and study process are shown in Fig. 1 and Table 1, respectively.

**Fig. 1 Fig1:**
[figure not shown]
Flowchart of the study procedure

**Table 1 Tab1:**
[figure not shown]
Study process of enrolment, intervention, and assessments

### Simple size

Campos DR et al. reported that the incidence of ICU-AW in the control group was P_1_ ≈ 0.45, and in the intervention group, it was P_2_ ≈ 0.11 [25]. According to those results, a sample size of 40 participants in each group was calculated to sufficiently detect the target effect size (0.5) with a type I error of 5% (*α* = 0.05) and 90% power (*β* = 0.10) by the PASS15.0 software. Allowing for a 20% loss to follow-up, this study was designed to include 80 cases.

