#### Primary outcome

##### MRC score

MRC score clinical assessments will be performed at baseline, and 7 days postintervention, MRC has proven to be a valid and reliable assessment scale to evaluate muscle weakness in critically ill individuals [30, 31]. MRC, as a convenient muscle strength assessment tool, is graded according to maximum muscle contraction, ranging from 0 to 5. The grade details are as follows: 0 = no contraction, 1 = visible and/or palpable contraction without limb movement, 2 = active movement, with gravity eliminated, 3 = active movement against gravity, 4 = active movement against gravity and submaximal resistance, and 5 = active movement against gravity and maximal resistance [32]. The MRC score was obtained by evaluating 6 groups of bilateral muscles. These include wrist dorsiflexors, elbow flexors, shoulder abductors, hip flexors, knee extensors, and ankle dorsiflexors. The total MRC score is 60, and higher MRC scores indicate better muscle strength [31].

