### Data collection and statistical analysis

Two trained evaluators will collect baseline data, outcomes, and follow-up data. Participant trial data will be recorded through the case report form. Participants will be informed of follow-up visits after discharge from the hospital, and follow-up data will be obtained through telephone questionnaires or home visits. Two investigators will check the case report form twice to ensure accuracy and completion and record the data of the case report form into the Excel file with double-check.

All participants can withdraw from the trial at any time. If participants terminate the trial or deviate from the intervention protocol, the investigators will record the trial data from the participant’s last intervention and report the reason for withdrawal.

The SPSS 26.0 software (IBM SPSS, Chicago, IL) was applied to analyze the baseline characteristics and outcomes between the two groups. *x̅* ± s will represent continuous variables that conformed to the normal distribution, and the *t* test will compare the differences between the two groups. The Mann–Whitney *U* test will be applied if continuous variables are not normally distributed. Categorical variables will be expressed as frequency (percentage, %), and the chi-square test will be used to compare the differences between the two groups. Effect estimates will be provided with corresponding 95% confidence intervals, and *P* values ≤ 0.05 will be considered significant. Aiming to preserve the unique benefit of randomization, regardless of whether that participant received the allocated intervention, the principles of intention-to-treat analysis will be used. All randomized participants will be included in the analyses, and data will be analyzed in the group in which the participants were originally randomized. All available data from the NMES group that was originally randomized will be analyzed as an intervention group, including participants from the NMES group who do not complete the NMES intervention or even do not receive NMES intervention. Similarly, all available data from the control group that was originally randomized will be analyzed as the control group, including any who receive the NMES intervention. Multiple imputation (MI) using the mice package in R will be applied to analyze the missing data.

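### The sample size and its 90% power are justified on ICU-AW incidence, which is not a listed outcome; the 90% is not shown for the MRC score comparison, and the effect size of 0.5 is undefined

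*Protocol article*

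**What the plan says.** The sample size section (headed Simple size) starts from a cited study. It states that "the incidence of ICU-AW in the control group was P_1_ ≈ 0.45" and that "in the intervention group, it was P_2_ ≈ 0.11". On the strength of those results it says that "a sample size of 40 participants in each group was calculated to sufficiently detect the target effect size (0.5", in parentheses and without a scale, "with a type I error of 5" per cent and 90% power. It then gives 80 cases in total, allowing for 20% loss to follow-up.

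The only primary outcome is the MRC score, at baseline and 7 days after the intervention. It sums graded strength over six bilateral muscle groups: "The total MRC score is 60, and higher MRC scores indicate better muscle strength".

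The data collection and statistical analysis section says of normally distributed continuous variables that the t "test will compare the differences between the two groups". The Mann–Whitney U test applies otherwise, and the chi-square test is kept for categorical variables. The safety section adds one interim analysis of the primary outcome at 40 participants, with a Pocock approach at an overall 0.05.

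**The concern.** A power figure belongs to one endpoint, one test and one assumed effect. Here the inputs are two proportions of patients with ICU-AW. That term appears only in the sample size section. It is not the primary outcome or any of the secondary outcomes, and no MRC cut-off turns the score into ICU-AW. The planned primary comparison is of a 0–60 score, for which no mean difference and no SD are given. Between the two stands an effect size of 0.5 that is said to rest on the cited incidences but matches no usual measure derived from them.

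The interpretation of the primary result is at stake. A non-significant MRC comparison would be reported from a trial described as having 90% power, although that power was not worked out for this comparison. The same outcome drives the interim analysis and the monitoring committee's advice to continue, modify or halt.

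**Working it through.** **Inputs.** From the sample size section: p1 = 0.45, p2 = 0.11, alpha 0.05, power 0.90, loss 20%, total 80. From the study design: 1:1 allocation. Sidedness is not stated; the analysis section says only that P "values ≤ 0.05 will be considered significant". I take two-sided and show one-sided where it matters.

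**1. Reproduce the 80.** Two proportions, unpooled variance:

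n = (p1q1 + p2q2)(z₀.₉₇₅ + z₀.₉₀)² / (p1 − p2)²

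- p1q1 + p2q2 = 0.45 × 0.55 + 0.11 × 0.89 = 0.3454
- (1.960 + 1.282)² = 10.507
- n = 0.3454 × 10.507 / 0.34² = 31.4, so 32 per arm
- 32 / 0.8 = 40 per arm, 80 in total

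This matches, reading the 40 per group as the number after the allowance for loss. Other two-sided formulas at 90% power give somewhat more after loss: arcsine 43 per arm, pooled 44, continuity-corrected 52 (86 to 104 in total). The 80 therefore belongs to a binary ICU-AW comparison.

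**2. Look for the 0.5 in the same rates.**

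| Measure | Calculation | Value |
|---|---|---|
| Risk difference | 0.45 − 0.11 | 0.34 |
| Cohen's h | 2·asin√0.45 − 2·asin√0.11 = 1.471 − 0.676 | 0.79 |
| w (phi) | 0.17 / √(0.28 × 0.72) | 0.38 |
| Shift of an underlying normal score | −0.126 − (−1.227) | 1.10 SD |

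None is 0.5. Nor does 0.5 lead to 80 on either natural scale. As w in a chi-square test it needs 43 in total for 90% power. As a standardised mean difference it needs 86 per arm by the exact t calculation (85 gives 89.99%), or 108 per arm after 20% loss.

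**3. Power of the MRC comparison.** The documents do not fix this, because they give no MRC difference and no SD. The range follows, using the noncentral t distribution with noncentrality d√(n/2) and 2n − 2 degrees of freedom. The Pocock rows use two equally spaced looks with critical value 2.178 and a normal approximation.

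| Scenario | 40 per arm | 32 per arm |
|---|---|---|
| d = 0.5, two-sided | 59.8% | 50.4% |
| d = 0.5, one-sided | 72% | 63% |
| d = 0.5, two-sided, Pocock | 56% | 47% |
| d = 1.10, two-sided | 99.8% | 99.1% |
| d = 1.10, two-sided, Pocock | 99.7% | 98.8% |
| d giving 90% power | 0.73 SD | 0.82 SD |
| d giving 90% power, Pocock | 0.76 SD | 0.85 SD |

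**4. How far apart the two targets are.** On the normal-score assumption, a shift of 0.5 SD from 45% gives Φ(−0.126 − 0.5) = 27% with ICU-AW, against the cited 11%. The two targets in the one paragraph, 0.5 and (as a shift) 1.10, differ by a factor of about 2.2.

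**The case against.** A reader might infer from the stated 0.5 that the trial simply has 50–60% power instead of 90%. The document does not support that as a plain statement, for three reasons.

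- The 0.5 is never called a standardised mean difference, and it follows directly on two proportions. Read as w for a two-group chi-square test, power would be 98% with 64 patients and 99% with 80.
- The 80 is correct for the stated incidences under a standard formula, so it cannot be called a miscalculation.
- If the cited effect is real and MRC scores are roughly normal, the implied shift of 1.10 SD would be detected with about 99% power.

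All three points stand, and they limit the finding to a conditional statement about power. It is also true that the MRC score and ICU-AW are related: the article introduces the scale as a measure of weakness in critically ill patients. The absence of a cut-off could be condensation in a journal article and carries little weight alone.

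None of this supplies the missing link. A related construct is still a different endpoint with a different test, and the 99% rests on a normal-score conversion that the protocol does not make. No reading of the 0.5 connects it both to the cited incidences and to the 80.

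**Conclusion.** The concern holds as a mismatch between the endpoint used for sizing and the endpoint analysed, together with an effect size that is undefined and cannot be derived from its stated source. It does not hold as an arithmetic error in the 80, nor as an unconditional statement that the trial is underpowered.

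The 90% is a property of an ICU-AW comparison that is not planned. For the planned MRC comparison, power runs from about 50–60% (47–56% with the Pocock boundary), if the target is 0.5 SD, to about 99%, if it is 1.10 SD. With 80 enrolled and 32 to 40 per arm evaluable, 90% is reached only from about 0.73–0.82 SD, or 0.76–0.85 SD with the interim look. These figures assume a two-sided test, approximate normality with a common SD, and equal arms. One-sided testing at 0.5 SD would still fall short, at 63–72%.

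This should be corrected, because the paragraph is the trial's stated justification for its size and does not apply to its primary analysis.

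**What to change.** Rewrite the sample size paragraph for the MRC comparison:

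- State the assumed between-group difference in MRC points and its SD, with their source, and the sidedness of the test.
- Report what 80 enrolled and 64 evaluable can detect with 90% power: about 0.82 SD (0.73 SD with no loss), or about 0.85 SD (0.76 SD) with the Pocock boundary.
- Define the 0.5 on a named scale, or remove it. Remove the 90% unless it is shown for this comparison.

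The cost is one paragraph and possibly a less favourable stated power. Enrolment need not change for the restatement. If the difference in MRC points then judged worthwhile lies below the detectable range, the team will have to accept lower power or revisit the number.

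The alternative is to keep the two incidences and make ICU-AW, at a stated MRC cut-off, the primary outcome with a two-proportion test, naming the formula that gives 32 per arm. That also keeps the 80, but it changes the primary outcome and so needs the protocol's amendment and ethics review steps.

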### Safety assessment and monitoring

NMES intervention will be carried out strictly based on the instrument operation specifications and implemented by two physiotherapists who have completed operation training. Patients will be informed of the potential adverse events of NMES and sign an informed consent form. Adverse events may occur during treatment: mean arterial blood pressure < 65 mmHg, 40 bpm < heart rate < 130 bpm, SpO_2_ < 88%, skin redness, skin burns, skin blisters, pain, myocardial ischemia, and arrhythmia. The NMES group will complete NMES therapy under the supervision of a physiotherapist. During treatment, any patient discomfort will be dealt with immediately (reduce the intensity of electrical stimulation or stop the intervention). The research team will judge the severity of adverse events and analyze the correlation with the intervention. Patients who suffer harm or complications caused by the intervention will receive medical treatment at the Second Affiliated Hospital of Chongqing Medical University free of charge. All serious adverse events will be reported to the ethics committee within 48 h.

Based on the sequential study design, the primary outcome will be analyzed when 50% of participants (40 participants) have randomly enrolled to complete the intervention and data collection. An independent statistician who is blinded to the intervention process will be responsible for performing the data analysis. Type I error statistical analysis will be performed using the Pocock approach with *α* = 0.05. The interim analysis results will be reported to the data monitoring committee (DMC). The DMC will access all data and discuss to decide whether the trial should be continued, modified, or halted earlier than intended.

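### The stated 90% power is that of a single test at α = 0.05; under the two-look Pocock rule that the protocol also prescribes, it is about 85–88% with the plan's own rates and 20% loss

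*Protocol article*

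**What the plan says.** All references are to the protocol article.

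*Simple size* takes its planning rates from an earlier trial: "the incidence of ICU-AW in the control group was P_1_ ≈ 0.45" and "in the intervention group, it was P_2_ ≈ 0.11". It then says that "a sample size of 40 participants in each group was calculated", "with a type I error of 5% (*α* = 0.05) and 90% power (*β* = 0.10) by the PASS15.0 software", and that 80 cases allow for 20% loss to follow-up. It mentions no interim analysis.

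*Safety assessment and monitoring* adds one. There, "the primary outcome will be analyzed when 50% of participants (40 participants) have randomly enrolled to complete the intervention and data collection", and "Type I error statistical analysis will be performed using the Pocock approach with *α* = 0.05". The result goes to the DMC, which discusses whether to continue, modify or halt.

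*Data collection and statistical analysis* sets the significance level at P ≤ 0.05 for all comparisons, without an exception for the primary outcome.

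**The concern.** The power and the testing rule belong to different designs. A Pocock rule spreads α = 0.05 over two looks, so the final test is stricter than 0.05. At an unchanged number of patients, some power is lost. If 80 patients were derived for one test at 0.05, the printed 90% does not describe the design that will be run.

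Pocock also places its boundary low at the first look. Under an effect as large as the planning rates, an early crossing is likely. If the DMC then halted, the secondary outcomes (diaphragm ultrasound, organ scores, Barthel Index to 6 months) would rest on about half the planned sample.

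**Working it through.** **Inputs.** From *Simple size*: rates 0.45 and 0.11, α = 0.05, power 90%, 40 per group, 20% loss. From *Safety assessment and monitoring*: one look at 40 of 80, Pocock, overall α = 0.05. Sidedness is not stated; two-sided is assumed.

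**Step 1: reproduce the plan's 40 per group.** For one test with unpooled variance:

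n = (1.960 + 1.282)² × (0.45×0.55 + 0.11×0.89) / 0.34² = 10.507 × 0.3454 / 0.1156 = 31.4, so 32 per group. Then 32/0.80 = 40.

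This matches, loss included. A continuity-corrected formula gives 41 per group before any loss, which is also close to 40. Both are single-look formulas.

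**Step 2: the Pocock boundary.** With the interim at information fraction t, the two statistics have means θ√t and θ, unit variance and correlation √t. The constant c solves P(|Z₁| < c, |Z₂| < c) = 0.95 at θ = 0. For t = 0.5, c = 2.178 (nominal P = 0.0294).

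**Step 3: any design with 90% single-look power.** Here θ = 1.960 + 1.282 = 3.242.

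- Two-look power is 1 − P(|Z₁| < c, |Z₂| < c) = 87.0%.
- The chance of crossing at the interim is Φ(3.242 × √0.5 − 2.178) = Φ(0.114) = 54.5%.

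**Step 4: the plan's rates, 32 evaluable per group (40 less 20%).**

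| Uncorrected test | One look | Pocock, look at 16 per group | Crossing at that look |
|---|---|---|---|
| Unpooled z, normal approximation | 90.5% | 87.6% | 55.4% |
| Pooled z, normal approximation | 87.6% | 84.2% | 51.0% |
| Chi-square, exact enumeration | 89.1% | 84.9% | 50.6% |

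**Step 5: timing of the look.** The text asks for 40 participants with complete data. If 64 are evaluable in the end, 40 completers give t = 40/64 = 0.625 and c = 2.156 (P = 0.031).

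- A 90% design then has 87.6% power and crosses at the interim with probability Φ(3.242 × √0.625 − 2.156) = Φ(0.407) = 66%.
- With the plan's rates, exact chi-square enumeration gives 86.9% power and 63.5% crossing. The two normal approximations give 84.9% and 88.2% power, with 62% and 67% crossing.

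**Step 6: readings with 40 evaluable per group.**

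- Uncorrected chi-square, exact: 94.5% for one look and 92.3% under Pocock.
- Continuity-corrected chi-square: 90.9% for one look and 87.7% under Pocock.

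**Step 7: Pocock at the interim, but P ≤ 0.05 at the end.** For a 90% design, power is 90.7% and the type I error is 6.7%.

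**Step 8: comparison boundary.** Two-look O'Brien-Fleming at t = 0.5 has a final c of 1.977 (P = 0.048). A 90% design keeps 89.8% power and crosses early 31% of the time.

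**The case against.** **The endpoint differs.** The interim tests the primary outcome, which is the MRC score, while the figures above use ICU-AW rates. This stands as a limit. The plan gives no MRC difference or SD, so neither power nor crossing probability can be computed for that score. The ICU-AW rates are nevertheless the only basis on which the 90% can be reproduced, and the fall from 90% to 87.0% follows for any approximately normal test statistic with 90% single-look power.

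**The shortfall depends on losses and on the test.** With all 80 evaluable and an uncorrected chi-square, power is 92.3%, above the stated figure. By normal approximation, Pocock power reaches 90% from about 35 (unpooled) or 38 (pooled) evaluable per group. This stands too, but the plan itself budgets for 20% loss. Multiple imputation keeps all patients in the analysis without fully restoring the lost information.

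**The loss arises only if the final test uses the Pocock value.** This is correct. With P ≤ 0.05 kept at the end, power stays at about 90%, but overall α is then about 6.7% rather than the 5% that the Pocock sentence promises. The plan cannot have both.

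**Stronger readings that the text does not support.** A reader might infer that the trial would stop at 40 patients about half the time. Crossing is not stopping: the DMC decides by discussion. The value near one half also belongs to a look at half the evaluable information; with 40 completers it is about 64–66%. A reader might also infer that Pocock is the wrong boundary. It is a legitimate choice, and thinner secondary data is a cost of any early efficacy stop. Nor is an unstated early-crossing probability a fault in itself, since an article commonly leaves it to the full protocol or SAP.

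**Conclusion.** The point holds, at modest size. The printed 90% is a single-look figure and is not a property of the two-look Pocock design described in the same article. A 90% design loses about 3 points, to 87%. With the plan's ICU-AW rates and 32 evaluable per group, power is about 85–88% across tests and timings of the look (84.2% at the lowest, by the pooled approximation).

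This rests on two-sided testing, on the plan's 20% loss or a continuity-corrected test at 40 evaluable per group, and on use of the Pocock threshold at the final analysis. A continuity-corrected test with only 32 evaluable per group is left out of the range: it gives 77%, but its single-look power is already 82%, so it is not a reading under which the stated 90% holds. The figures concern the rates used for sizing and make no statement about the MRC score.

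**What to change.** Two wording changes, with no extra patients:

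1. In *Simple size*, restate the power as that of the two-look Pocock rule at the evaluable number (about 85–88% for 0.45 v 0.11 with 32 per group). Name the test and the sidedness, and say that the figure refers to ICU-AW.
2. In *Data collection and statistical analysis*, replace P ≤ 0.05 for the primary outcome with the Pocock final threshold: about 0.029 if the look falls at half the information, or 0.031 if it falls at 40 of 64 evaluable patients.

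The cost is a printed power a few points lower.

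Two alternatives are design choices rather than corrections. An O'Brien-Fleming boundary with the look at half the information (final P about 0.048, also written into the analysis section) keeps 89.8% power where the fixed design has 90%. Its cost is a lower chance of early efficacy crossing, about 31% instead of 55%. Keeping both Pocock and 90% needs about 10% more patients: 31.4 × 1.10 = 34.5, so 35 evaluable per group; 35/0.8 = 43.75, so 44 per group, or 88 in total.

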### Randomization

Numbers 1 to 80 will be randomly divided into the NMES group and control group using the SPSS 26.0 (IBM, USA) software by two investigators who were not involved in the trial. Another two investigators will make envelopes to hide groupings. The number can be seen on the surface of the envelope, but group information is inside the envelope. To ensure that the trial is blind, only investigators will have the authority to access envelope information. Eligible patients will be numbered in the order of the time they participated in the trial, and the investigators will open the envelope according to the patient number to determine the grouping of patients and further arrange for the patient to receive corresponding trial interventions.

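### The sample size paragraph gives 80 both as the calculated requirement and as the total after a 20% loss allowance; one statement is wrong, and 90% power does not survive the loss plus the planned interim look

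*Protocol article*

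**What the plan says.** All the figures are in the protocol article's section headed Simple size. It takes two incidences of ICU-acquired weakness from a cited study: "the incidence of ICU-AW in the control group was P_1_ ≈ 0.45, and in the intervention group, it was P_2_ ≈ 0.11". From these it reports that "a sample size of 40 participants in each group was calculated", at a 5% type I error and "90% power (*β* = 0.10) by the PASS15.0 software". The closing sentence is "Allowing for a 20% loss to follow-up, this study was designed to include 80 cases".

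The rest of the article treats 80 as the number randomised. The Randomization section has "Numbers 1 to 80 will be randomly divided into the NMES group and control group", and the Abstract and Study design give the same total with 1:1 allocation. No smaller number before loss appears anywhere.

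Two other places bear on power. The statistical analysis section names the chi-square test for categorical variables. The section on safety assessment and monitoring plans an interim analysis of the primary outcome once 40 participants have completed the intervention and data collection, using the Pocock approach with alpha 0.05.

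**The concern.** A loss allowance has to make the recruited number larger than the calculated one. Here 40 per group, or 80 in total, is the output of the calculation, and 80 is also the figure after the allowance. Both statements cannot be true.

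What is at stake is the number of evaluable patients behind the 90% claim. It is 80 on one reading and 64 on the other (80 × 0.8). Until that is settled, neither the sponsor nor the data monitoring committee, which is asked to watch the dropout rate, can tell whether 20% loss is already covered or eats into the power. An analysis plan written later would inherit the contradiction rather than resolve it.

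**Working it through.** **Inputs.** p1 = 0.45, p2 = 0.11, alpha 0.05, power 0.90 and loss 20% (section Simple size); 1:1 allocation (Study design); chi-square test (statistical analysis section); one interim look at half the patients with Pocock (safety section). Two-sided testing is assumed, because the sample size section does not state it. The Pocock nominal level for two equally spaced looks is taken as 0.0294 per look; the article does not print it.

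**Step 1: can 40 per group be reproduced?** The difference is 0.34, squared 0.1156. The sum of variances is 0.45 × 0.55 + 0.11 × 0.89 = 0.3454. (1.960 + 1.282)² = 10.507. After-loss numbers are n/0.8, rounded up.

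| Formula | n per group | After 20% loss |
|---|---|---|
| Unpooled: 10.507 × 0.3454 / 0.1156 | 31.4 → 32 | 40 |
| Arcsine | 33.3 → 34 | 43 |
| Pooled: (1.960·√0.4032 + 1.282·√0.3454)² / 0.1156 | 34.5 → 35 | 44 |
| Pooled, continuity-corrected | 40.2 → 41 | 52 |

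So 40 arises in two ways. It is the number after loss by the unpooled formula, exactly. It is also, within one patient, the number before loss by the continuity-corrected formula.

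**Step 2: what each reading implies.**

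- If 40 is the evaluable requirement: 40/0.8 = 50 per group, 100 in total. Recruiting 80 includes no allowance.
- If 80 includes the loss: 40 × 0.8 = 32 per group was the requirement, and the sentence giving 40 as the calculated size is wrong.

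**Step 3: power at a flat two-sided 0.05, for 0.45 versus 0.11.** The unpooled normal figure at 32 is Φ(0.34/√(0.3454/32) − 1.960) = Φ(1.31) = 90.5%. The chi-square and Fisher figures are exact sums over all binomial outcomes.

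| Test | 32 per group | 40 per group |
|---|---|---|
| Unpooled normal | 90.5% | 95.5% |
| Chi-square, exact | 89.1% | 94.5% |
| Pooled normal | 87.6% | 93.8% |
| Fisher exact (not named in the article) | 83.3% | 91.3% |

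**Step 4: power with the Pocock interim look.** Each look rejects if |Z| exceeds 2.178 (nominal 0.0294). With 20% loss the looks fall at 16 and 32 evaluable per group.

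- Chi-square, exact: 83.4% if only the final look is counted, and 84.9% when rejection at either look is credited.
- Unpooled normal approximation: 86.3% at the final look and 87.6% over both looks.
- With no loss (looks at 20 and 40 per group), the chi-square test has 92.3% over both looks.

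So 90% is reached under the interim plan with 40 evaluable per group, but not with 32.

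**The case against.** The strongest reply is that the paragraph is only badly worded. The one formula that gives exactly 40 from the stated rates already includes the loss (32/0.8 = 40); the route without loss gives 41 after rounding up. At 32 per group that same formula has 90.5% power, and the planned chi-square test is about one point short of 90% at a flat 0.05. This stands. A reader might infer that the allowance is definitely missing, that 100 patients are needed, or that 90% power is lost outright. The documents support none of these as a certainty.

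It is also fair that the 20% may refer to follow-up up to six months after discharge, whereas the primary MRC score is measured after seven days of intervention. The article does not say when the loss occurs, so 32 evaluable per group for the primary outcome is an assumption. Intention-to-treat analysis with multiple imputation keeps everyone in the analysis set, but it does not in general restore lost information.

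The interim look is a separate design feature, and the cost it adds does not come from the loss arithmetic. It belongs here only because any power restated at 32 per group has to be the power under the boundary the trial will use.

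A reader might also bring in the target effect size of 0.5. Its scale is not defined and it is not the difference between the two rates (0.34). That is a different problem, and no figure based on it is used here.

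**Conclusion.** The contradiction is certain: one of the two sentences about the sample size is wrong. Which one cannot be told from the article, although the stated rates fit 32 before and 40 after loss exactly.

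The loss of power is modest and conditional. With 32 evaluable per group and the cited rates, 90% is marginal at a flat 0.05 (about 88–91%). It is not kept under the planned interim look: about 85% for the chi-square test, and 87.6% by the most favourable approximation. These figures assume two-sided testing, 20% loss applied equally at both looks and in both groups, and a comparison of the two incidences on which the calculation was built.

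**What to change.** Rewrite the sample size paragraph so that it gives the PASS procedure, the test and its sidedness, and the number per group before and after the loss allowance. There are two consistent versions:

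1. Keep 80 randomised (40 per group), state that 32 per group are expected to be evaluable after 20% loss, and give the power at 32 per group under the Pocock boundary (about 85% for the chi-square test with the cited rates).
2. State that 40 evaluable per group are needed, that 80 contains no loss allowance, and give the lower power that follows if 20% are lost.

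The sponsor knows which matches the calculation that was run. Either is a change of wording, with no effect on the number randomised, the randomisation list or the analysis. The cost is a less favourable stated power.
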